#### Dutch RCT

All women living in the Northern region of the Netherlands aged between 18 and 45 years who want to become pregnant within 12 months are eligible for participation in the study.

Women are excluded if they: (a) had previous offspring with NTD, (b) do not give informed consent, (c) do not understand Dutch, (d) plan to move to an area where the study is not implemented, (e) use FA antagonists, (f) are affected by diabetes, megaloblastic anaemia and/or cancer (previous cancer or abnormal PAP smears), (g) are already pregnant at the time of inclusion or within 4 weeks after the start of the intervention, (h) take high doses of FA for any other reason.

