However, studies conducted in Europe failed to find an optimal level of serum folate in these populations
[112,118] and recent data suggest that pregnant women use high doses of FA supplementation in early- to mid-pregnancy in several European countries
[75,79,119].

The standard recommendation for the recurrence prevention of NTDs and to prevent their occurrence in epileptic and diabetic mothers is to take a higher dose of FA, 4–5 mg/day
[111]. Furthermore, in 2007 the Canadian Recommendations also included obesity (BMI >35) as a health risk and recommended "the higher dose FA strategy (5 mg)" in patients with a history of poor compliance with medications and additional lifestyle issues of variable diet, no consistent birth control, and alcohol, tobacco, and recreational non-prescription drugs use
[120,121]. In particular, the use of FA supplements might (partially) neutralize the adverse effects of smoking on DNA methylation, since folate provides methyl groups for the synthesis of methionine and plays a critical role in homocysteine metabolism
[122-124].

Moreover, women planning to become pregnant might be exposed to medications with known antifolate activities affecting different parts of the FA metabolic cascade. Epidemiological studies have shown an increased risk of birth defects or placenta-mediated adverse pregnancy outcomes among women exposed in early gestation to antiepileptic drugs (carbamazepine, valproate, barbiturates), sulphonamides or methotrexate
[125,126]. Hence, whenever women use these medications, or have used them in the period prior to conception, they should take 5 mg/day of FA until the end of the first trimester of pregnancy
[121].

Wald et al.
[112] addressed the issue of the efficacy of high FA dosage more comprehensively, assessing the effect of increasing FA intake on serum folate levels and on the relation between these levels and the risk of having NTDs during pregnancy. They found that from a typical western background serum folate level of 5 ng/mL, an increase of 0.4 mg/day would reduce the risk of NTDs by about 36%, while taking 5 mg/day would reduce the risk by about 85%. A working group convened by the WHO Regional Office in Europe and Istituto Superiore di Sanità on 11–12 November 2002 endorsed these estimations
[127].

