Actually there is no good evidence to advise a different dose to women without an increased risk, women with a foetal NTD during a previous pregnancy or women with another well-known risk factor. If a dose of 4–5 mg/day can prevent recurrence or occurrence in women with well-known risk factors, it should be the same for the occurrence and in women with no known risk factors.

The question remains concerning the best dose of FA supplementation, as the prevalence of CMs worldwide is still high.

Overall, from all these studies it can be speculated that an increased peri-conceptional intake of FA can cause a greater reduction in the risk of NTDs as well as a greater and measurable reduction in the risk of other CMs, including trisomy 21 syndrome.

The hypothesis that a higher intake of FA is related to a higher risk reduction of NTDs and of other CMs is the main rationale for the Italian and Dutch RCTs.

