#### Dutch RCT

The study is an RCT, with four intervention arms. Initially, two groups are formed: 4.0 mg FA *vs* 0.4 mg FA supplementation peri-conceptionally and both of those groups will be split at 12 weeks of gestation into a group with 0.2 mg FA until the end of pregnancy and a group with 0.8 mg FA until the end of pregnancy:

1) 0.4 mg of FA from 4 weeks pre-conception to 12 weeks of gestation, and 0.2 mg FA supplementation after 12 weeks of gestation;

2) 0.4 mg of FA from 4 weeks pre-conception to 12 weeks of gestation, and 0.8 mg FA supplementation after 12 weeks of gestation;

3) 4.0 mg of FA from 4 weeks pre-conception to 12 weeks of gestation, and 0.2 mg FA supplementation after 12 weeks of gestation;

4) 4.0 mg of FA from 4 weeks pre-conception to 12 weeks of gestation, and 0.8 mg FA supplementation after 12 weeks of gestation.

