### Study population

#### Italian RCT

Women of childbearing age, 18–44 years, who intend to become pregnant within 12 months are eligible for the study. All eligible women who show up at obstetric and gynaecological clinics, assisted reproduction centres, family planning services, general practitioners and paediatricians are invited to visit the randomization centres for a complete pre-conception counselling and a talk about participating in the study.

Women are excluded if they: (a) are pregnant, (b) do not intend to become pregnant, (c) are younger than 18 and older than 44 years, (d) are planning to move to an area where the study is not implemented, (e) do not understand Italian, (f) do not have a phone, (g) are affected by epilepsy, even not treated with anti-convulsant drugs, (h) are affected by diabetes, (i) have suffered from cancer or a serious disease (e.g.: Crohn disease, rheumatoid arthritis, ulcerative colitis), (j) are being treated with antifolates or have recently been treated with it, like methotrexate, (k) abuse or have abused alcohol, (l) are obese (BMI ≥30), (m) are vegetarian, (n) had a previous pregnancy with NTD or any other congenital structural birth defects, (o) are affected or have a partner that is affected by NTD, have a relative (in her family or in the partner’s family) affected by NTD, (p) have a family medical history of breast cancer or colorectal cancer, (q) have a personal or family history of an hereditary syndrome like familiar adenomatous polyposis or hereditary nonpolyposis colorectal cancer, (r) report allergy to FA, (s) present contraindications to FA use, (t) are affected by megaloblastic anaemia, (u) take defined dosages of FA for directions other than those listed in the above exclusion criteria.

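### The Dutch exclusion list does not name epilepsy, so a woman with untreated epilepsy who is not already on high-dose folic acid has a 50% chance of 0.4 mg, below the article's own standard for her (minor)

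*Protocol article*

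**What the plan says.** All references are to the protocol article.

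- **Background, Peri-conceptional FA supplementation.** One sentence sets a single dose, 4–5 mg/day, for three groups. It opens "The standard recommendation for the recurrence prevention of NTDs and to prevent their occurrence in epileptic and diabetic mothers". The same section links birth defects and placenta-mediated outcomes to early exposure to "antiepileptic drugs (carbamazepine, valproate, barbiturates), sulphonamides or methotrexate".
- **Background, Folic acid supplementation.** Anti-convulsants are listed as a class among the drugs that interfere with folate.
- **Study population, Dutch RCT.** Criterion (a) excludes women who "had previous offspring with NTD". The next relevant criteria read "e) use FA antagonists, (f) are affected by diabetes, megaloblastic anaemia and/or cancer". Criterion (h) excludes women already taking high doses of FA for some other indication. None of the eight criteria, (a) to (h), names epilepsy.
- **Study population, Italian RCT.** Criterion (g) excludes women who "are affected by epilepsy, even not treated with anti-convulsant drugs". A separate criterion (j) excludes those who "are being treated with antifolates or have recently been treated with it, like methotrexate".
- **Study design and Randomization procedures, Dutch RCT.** Women are allocated equally to four groups. Groups 1 and 2 take 0.4 mg up to 12 weeks; group 2, for example, takes "0.4 mg of FA from 4 weeks pre-conception to 12 weeks of gestation, and 0.8 mg FA supplementation after 12 weeks of gestation". Groups 3 and 4 take 4.0 mg over the same period.

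**The concern.** The article names three kinds of women for whom 4–5 mg/day is already the standard, and the Dutch trial randomises between 4.0 mg and 0.4 mg. For two of the three, the Dutch list avoids random allocation to the low dose by excluding them. For the third, no criterion names the condition.

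What is at stake is the protection of individual participants. A woman with epilepsy who meets no other exclusion could be given, under blinding, a dose that the trial's own rationale treats as too low for her during the weeks when NTDs arise.

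**Working it through.** **Plan's own figure.** This point depends on no computed figure. The only one in the article, about 1,000 pregnancies (Sample size), is reproduced for 30% versus 22%, two-sided alpha 0.05 and 80% power with continuity correction: 496 per group, 992 in total. Adding an exclusion criterion does not change it.

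**Step 1. Match the high-dose groups to the Dutch criteria.**

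| Group with a 4–5 mg/day standard | Dutch criterion | Italian criterion |
|---|---|---|
| Recurrence prevention of NTDs | (a) | (n) |
| Diabetic mothers | (f) | (h) |
| Epileptic mothers | none by name | (g), treated or not |

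Two of the three groups are excluded by name and one is not.

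**Step 2. See what the other Dutch criteria remove.**

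- *Criterion (e), FA antagonists.* On a narrow reading this covers carbamazepine, valproate and barbiturates, the antiepileptics named in the peri-conceptional section. On a broad reading, taking the class listing in the earlier Background section, it covers every woman currently on an anticonvulsant. On neither reading does it reach an untreated woman.
- *Criterion (h), high-dose FA.* This removes women who already take the higher dose. It does not remove women who should take it but do not. Recruitment, Dutch RCT, says individual pre-conception care is not widely available in the Netherlands, so earlier high-dose advice cannot be assumed.
- *General practitioner involvement.* The pharmacist and the woman's general practitioner both take part in inclusion, but the printed list gives them no epilepsy criterion to apply.

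**Step 3. Define the remaining group.**

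- Under either reading of (e): untreated epilepsy, not already on high-dose FA.
- Under the narrow reading only: in addition, women on other antiepileptics who are not already on high-dose FA.

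**Step 4. Chance and size of the lower dose.**

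- P(0.4 mg) = groups giving 0.4 mg / all groups = 2/4 = 50%. With the exclusion added it would be 0.
- Dose relative to the standard: 0.4/5 = 8%; 0.4/4 = 10%.

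**Step 5. Number of women, by assumption only.** The article gives no count. Suppose 0.1% to 0.5% of Dutch women randomised fall in the remaining group (assumption).

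- Per 1,000 randomised: 1,000 × 0.001 × 0.5 = 0.5, and 1,000 × 0.005 × 0.5 = 2.5 women on 0.4 mg.
- About 1,000 pregnancies at a pregnancy rate of 80–85% imply 1,000/0.85 ≈ 1,176 to 1,000/0.80 = 1,250 women, say 1,200. If that total covers both trials and half are Dutch (two further assumptions), 600 women give 600 × 0.001 × 0.5 = 0.3 to 600 × 0.005 × 0.5 = 1.5 women on 0.4 mg.

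**The case against.** **Criterion (e) may already cover every treated woman.** The article lists anti-convulsants as a class that interferes with folate, and nothing says that the three named drugs are a complete list. This stands. A reader might infer that treated women with epilepsy are generally left in the trial, and the article does not support that. But the earlier listing does not define (e) either, since it also includes oral contraceptives, so which treated women are removed stays open.

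**Support for untreated epilepsy is thin.** The mechanism the article describes is drug exposure, and the recommendation rests on a cited source that is not available here. This stands in part. The sentence speaks of epileptic mothers without mentioning treatment, however, and the Italian list excludes the condition itself in addition to antifolate drugs. The joint project therefore did not consistently regard a drug criterion as enough.

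**The Italian list is not a benchmark.** The trials are registered separately, and the Dutch list also omits obesity, vegetarian diet and alcohol abuse. This is fair: a difference between the lists is not in itself an error. The point rests on the Dutch list set against the article's own recommendation. The Italian criterion only supplies ready wording.

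**The article doubts risk-specific dosing.** It does say the evidence for differing doses is poor. Its conclusion is that if 4–5 mg works in women with known risk factors, "it should be the same for the occurrence and in women with no known risk factors". That argues for raising the dose in low-risk women, not for lowering it in women at risk. The Dutch list still excludes previous NTD offspring and diabetes, so it does not act on that doubt.

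**An article condenses the full protocol.** This is true, and the full Dutch protocol may name epilepsy. But the article prints a lettered list that covers two of three groups from one recommendation, so the mismatch is on the page. A reader might also infer that (e) is defective because, unlike Italian (j), it does not mention recent use. That is not supported: a look-back period is the kind of operational detail an article leaves to the full protocol.

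**Conclusion.** The point holds as a minor matter of participant protection. As printed, the Dutch criteria leave eligible a woman with untreated epilepsy who is not already on high-dose FA. If (e) is read narrowly, they also leave eligible a woman on an antiepileptic other than those named. Her chance of 0.4 mg is 50%. The percentage of the standard dose describes the shortfall; it is not an estimate of harm.

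The number of such women is not in the document and is probably very small. The figures per 1,000 randomised rest wholly on an assumed share.

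A reader might infer that the omission distorts the comparison of doses. It does not: allocation within the Dutch trial is random whatever the epilepsy status, and sample size and analysis are unaffected.

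The conclusion assumes that the printed list is the one applied and that the recommendation for epileptic mothers includes those not on drug treatment.

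**What to change.** Add a Dutch exclusion for women affected by epilepsy, treated or not, matching Italian criterion (g). If the full Dutch protocol already excludes epilepsy, a one-line correction to the published list is enough. If not, it takes one eligibility amendment, which is still worthwhile because the article describes the project as ongoing.

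The cost is one screening question and a few eligible Dutch women lost to a trial that is already recruiting slowly. Criterion (e) can stay as worded, because naming the condition makes its reach irrelevant for epilepsy. Sample size and analysis do not change.

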### Recruitment

#### Italian RCT

In Italy, as well as in other countries, there is no recognized clinical activity defined as "pre-conceptional counselling". All women planning their pregnancy who discuss their intention to hospital and community gynaecologists, general practitioners, paediatricians, and obstetricians in the various areas of Italy are invited to refer to the randomization centres to receive fully structured pre-conceptional counselling according to the standard recommendations and, if consenting, to be recruited into the study and randomized.

The invitation is particularly focused on making the woman and the couple aware of the importance of complete pre-conceptional counselling, as a means of reducing possible adverse events in the human reproduction process. FA supplementation is one of the actions promoted by the pre-conceptional counselling. The recruiting investigators explain such preventive intervention and its objectives to the women and highlight the possibility to participate to the randomized study. The invitation to contact the randomization centres is reinforced by an ad hoc informative sheet.

The randomization centres are obstetric and gynaecological clinics, assisted reproduction centres, family planning services, and general practitioners.

#### Dutch RCT

In the Netherlands, eligible women are primarily approached through proactive recruitment campaigns conducted by community pharmacies (CPs). Inclusion takes place in a coordinated campaign run by the community pharmacists and the general practitioner of the participant.

Since individual pre-conception care is currently not available on a large scale in the Netherlands, no "natural" existing starting point for the recruitment procedure is available. The target population from which the actual recruitment has to take place consists of all women of childbearing age that have the intention to become pregnant within the next 12 months. The actual inclusion (final step of the recruitment process) mainly takes place during CP visits, in which consent is given.

Personal informative mailings from CPs are sent to all female clients in the age group 25–35, accompanied by a letter that requests, if appropriate, considering participation in the trial on behalf of the pharmacist. In addition, permanent public information are present in the CP and recurrent personal information are given at delivery of certain Over-The-Counter and prescribed drugs in the CP. Other health professionals contribute towards informing the target group: posters and leaflets are available at well baby clinics and with primary care physicians. At some sport schools and child care centres posters are present. Representatives of the research team promoted participation in the trial and gave information at fairs targeted at women of reproductive age.

### Randomization procedures

#### Italian RCT

After giving informed consent, women are randomly assigned to receive a pill containing 4 mg of FA (treatment in study) or 0.4 mg of FA (referent treatment) daily. The randomization code is generated by a web-based patient randomization system, stratified according to the enrolment site and the maternal age group. The study is double-blinded: subjects, investigators and research staff are blinded to the randomization assignments.

#### Dutch RCT

After giving informed consent, women are randomized to one of the four groups. Randomization is not stratified. Every four participants per research centre are assigned to a different study group, resulting in equal distributions among the study groups. The study is double-blinded: subjects, investigators and research staff are blinded to the randomization assignments.

### Interventions

#### Italian RCT

At the enrolment visit, full pre-conceptional counselling is offered to women according to standard guidelines. All the eligible women are interviewed by the investigators using a structured form to evaluate socio-demographic and lifestyle characteristics, past and present health status, previous pregnancy outcomes, and the previous four months of food intake.

Subjects who show interest in participating in the study and who meet the inclusion criteria, in the absence of exclusion criteria and after giving informed consent, are randomized to either 4 mg or 0.4 mg of FA.

All women are given a box containing 130 pills, according to the blinded randomization arm. All women are then recommended to take one pill per day and to contact the enrolment centre when only 20 pills are left in the box so that they get another box of 130 pills. After randomization, enrolled women are interviewed every 4 months by the investigators (when they contact the randomization centre to get another box of FA pills), to evaluate the pregnancy status.

If women become pregnant, they will take the FA until the end of the 12th completed gestational week. If they have not become pregnant after 12 months of FA supplementation, the women will be removed from the study.

#### Dutch RCT

Women in all intervention groups receive identical pills, containing two different doses of FA (4 or 0.4 mg). Women start taking the pills after randomization, but at least 4 weeks before conception, and will receive new pills from their pharmacy every 4 months.

At 12 weeks of gestation, all women will receive a new set of pills, half of them receiving 0.2 mg supplements and half 0.8 mg of FA. Again the pills are identical. New pills are issued once more during pregnancy (25 weeks of gestation).

### Information collected and follow-up

#### Italian RCT

At the enrolment visit, all the eligible women are interviewed by the investigators using a structured form to evaluate socio-demographic and lifestyle characteristics, past and present health status, previous pregnancy outcomes, and the previous four months of food intake.

After randomization, enrolled women are interviewed by the investigators every 4 months (if not pregnant), when they contact the randomization centre to get another box of FA pills. The interview at 4-8-12 months is performed using a structured form to evaluate the pregnancy status, current health conditions, and experimental medicine intake.

Enrolled randomized women who are diagnosed as being pregnant during the study period and who take the FA until the end of the 12th completed gestational week, are invited to come back to the randomization centre to return the remaining pills and to update their status.

They will be interviewed at the expected 16, 24 and 40 weeks of gestation by a trained Health Care Provider (HCP) by phone using a structured form to evaluate the pregnancy outcome. All the pregnancy outcomes, irrespective of the information reported by the woman at the interview, will be checked in the hospital’s clinical records by a trained HCP.

The health status of live births will be evaluated by a trained HCP through an interview with the attending physician using a structured questionnaire when the child reaches the age of 1 month, 3 months and 1 year, and an interview with the parents when the child is 1 year old.

#### Dutch RCT

Most data are gathered through questionnaires in the Netherlands. Information on all CMs of live births, stillbirths and terminations of pregnancy following prenatal diagnosis are derived from the database of EUROCAT, where virtually all CMs are registered. Data about the diagnosis and the medical history are collected in a standardized procedure of high quality.

Variables derived from medical records are: birth weight, gestational age, diseases during pregnancy (diabetes, high blood pressure), abruptio placentae, Apgar score.

In a short questionnaire, women answer questions on compliance to trial medication, the use of vitamin supplements and the use of alcohol, tobacco and drugs. These questions will be repeated each time they pick up their supplements at the pharmacy.

Follow-up: after randomization, women receive a new set of pills every 4 months at the pharmacy, until a period of 12 months has elapsed without them getting pregnant or until the end of their pregnancy (live birth, stillbirth, spontaneous abortion or termination). After the pregnancy has been completed, women and their general practitioners will receive a final questionnaire about pregnancy outcomes by mail.

### Definition of treatment compliance and withdrawal

#### Italian RCT

Compliance to FA supplementation is evaluated by counting the pills not taken and that remain in the given box at the randomization centre.

Three categories will be defined for compliance status: (a) fully treated women: those women who will take at least 70% of the expected pills during the full peri-conceptional period (1 month before and 3 months after last menstruation); (b) partially treated women: women who will take between 30% and 69% of the pills during the full peri-conceptional period, (c) non-treated women: less than 30% of the pills. The last category will be considered as non-compliant.

Patients may be withdrawn and excluded from the "protocol analysis" but evaluated at the "intention-to-treat" analysis for any of the following reasons: any protocol violation, non-compliance, lost to follow-up, patient withdrawn at her own request, for reasons other than those above.

